### 2.2. Study Settings

According to our pilot study, we evaluate the time required by the participant at about 15 min per phase.

For the first phase, investigators will assess the Karasek’s questionnaire, food intake questionnaire, Maslach Burnout Inventory, and Hospital Anxiety Depression Scale (HAD) among Emergency health care workers at the beginning of the control day (around 8:30 am). A sample of saliva in an Eppendorf will be recovered at the same time. Saliva collection will be brought in a cooler to the Institute of Occupational Medicine of Clermont-Ferrand by the end of the day. The samples will be stored at −80 °C. The experimenter will also deliver a pre-stamped envelope for the return of 2 Eppendorf tubes (saliva collection) and questionnaires at the end of the day.

Considering the difficulties of obtaining homogenous planning with all emergency providers, the time passed between the first and the second phase will not be the same between all providers. However, the 2 phases need to be separated by at least 1 week.

For the second phase, investigators will assess the same questionnaires with the saliva collection at the beginning and the end of a 24-hour or 14-hour nightwork session (up to 1 week later). This will permit the evaluation of the relationships between modifications in questionnaire answers and biological responses by comparing results during a control day versus results at the end of a work session, including a nightshift.

The third phase of the SEEK protocol is a longitudinal follow-up. This study design will be reproduced every 5 years in all Emergency Departments. If possible, i.e., if they are already in the same Emergency Department, we will follow-up on the initial cohort. We choose a follow-up of 5 years because it corresponds to the residency program duration in Emergency Medicine in France. We will program 4 sessions for a total of 20 years.

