## 3. Results

### 3.1. Justification of the Sample Size

The number of subjects required justification is based on the ability to recruit participants, namely 120 subjects. Previous studies have shown an acceptance rate above 80% in the emergency health care workers’ population; power estimates will be provided based on 100 subjects included. In addition to the expected variability, this type of study can have a fixed margin of error on the estimated sample size (reliability of the sample). Referring to the data of our pilot study, the Karasek questionnaire found low decision latitude (59.67 ± 6.44, 6% higher than 71), a significant psychological burden (29.39 ± 4.07; 94% greater than 20), and high social support (29.94 ± 3.21, 100% above 24), meaning that with at least 100 subjects considered, the error margin will be very satisfying that is respectively ±1.25, ±0.8 and ±0.63. If we consider the different dimensions score as categorical (<> 71 <> 20 and <> 24), accuracy will be ±5% with n = 100.

Furthermore, simulations on secondary objectives can complete this justification. To see a change in the emergency health care workers’ work perception during a control day versus the results at the end of a nightshift, 100 subjects will show minimum differences of the order of 2.35, 1.48, and 1.17 for decision latitude dimensions, psychological demand, and social support, with a type 1 error risk of 5%, a power of 95% and a correlation coefficient of 0.5 (matched condition).

With 100 subjects, and given the assumptions described above, 5 predictors can be explored to identify factors that explain emergency work perception for a power greater than 80% [47].

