### 3.3. Data Analysis

Continuous variables will be presented as mean and standard-deviation or median and interquartile range according to the statistical distribution. The normality assumption will be assessed using Shapiro–Wilk test. Categorical variables will be expressed as numbers and associate percentage. The primary analysis will be mainly descriptive and will define the perception scores of emergency physicians work according to the Karasek questionnaire for each dimension composing the score (decision latitude, psychological demands, and social support), as quantitative and categorical variable. A correlation matrix analysis on quantitative variables (i.e., Karasek questionnaire and other psychological questionnaires) will be conducted using Pearson or Spearman correlation coefficients, in addition to principal component analysis (PCA). The Karasek questionnaire score’s evolution, obtained for each dimension, will be tested with a paired two-sample Student’s test, or nonparametric Wilcoxon test if necessary. Linear regression models and random-effects models will complete these analyses. These models will permit, with multivariable analyses and covariates’ introduction, to seek possible explanatory factors of the Karasek score (a dayshift (control) versus the end of 24 h or shift) and its evolution. The same statistical analysis plan will be used for continuous parameters collected after the dayshift (control) and after the 24-h shift (e.g., all biological samples). For categorical variables, Stuart-Maxwell test will be used. The comparisons for quantitative parameters (e.g., biological data, questionnaires’ scores) will be based on Student’s *t*-test or nonparametric Mann–Whitney test. The comparisons involving categorical parameters (gender, seniority) will be made with the Chi-squared test or Fisher’s exact test. All statistical analyses will be performed as two-sided tests, with a *p* < 0.05 considered as significant. Statistical analyses will be performed using the Stata software (version 16, StataCorp, College Station, TX, USA).

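### The named test of the short-term Karasek change uses complete pairs only; the random-effects model the plan already lists would be the safer main test

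*Protocol article*

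**What the plan says.** Section 3.3 (Data Analysis) of the protocol article fixes the test of change: for each dimension, the evolution of the score "will be tested with a paired two-sample Student’s test, or nonparametric Wilcoxon test if necessary". It continues: "Linear regression models and random-effects models will complete these analyses". The stated purpose follows: "These models will permit, with multivariable analyses and covariates’ introduction, to seek possible explanatory factors of the Karasek score", on the control dayshift versus the end of the shift, and of its evolution. The general rule is "All statistical analyses will be performed as two-sided tests, with a *p* < 0.05 considered as significant". The section extends the same approach to other continuous measures taken on both occasions, including the biological samples.

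Section 2.2 (Study Settings) has investigators collect the control-day questionnaires and saliva at about 8:30 am. In the same first-phase paragraph, the experimenter will "deliver a pre-stamped envelope for the return of 2 Eppendorf tubes (saliva collection) and questionnaires". The second phase repeats the questionnaires and saliva at the beginning and end of a 14-hour or 24-hour session. Section 3.2.8 says samples taken after the work session are posted.

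Section 3.1 sizes the comparison: "100 subjects will show minimum differences of the order of 2.35, 1.48, and 1.17 for decision latitude dimensions, psychological demand, and social support". Those differences assume a 5% error rate, 95% power and a within-person correlation of 0.5. The change between occasions is a secondary objective (end of Section 1); the primary analysis is mainly descriptive.

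**The concern.** A paired t-test or Wilcoxon test needs both scores from the same worker. A worker assessed on the control day whose end-of-session form never arrives contributes nothing, although half of that worker's information is in hand. If absence is unrelated to the control-day score, only precision is lost.

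If absence is related to that score, the workers who remain are a selected group at the first measurement. With a correlation below 1, a group selected for high scores tends to fall at the second measurement and a group selected for low scores tends to rise, without any effect of the nightshift. The paired test reads this regression to the mean as change, and its nominal 5% error no longer holds.

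The plan already names a class of model that can keep the unpaired control-day scores. As written, that model is not given the job of estimating the nightshift change.

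**Working it through.** **Inputs from the article.** SDs 6.44 (decision latitude), 4.07 (psychological demand) and 3.21 (social support), correlation 0.5, power 95% and 100 subjects (Section 3.1); two-sided 5% (Section 3.3); 120 recruited (Section 2.5).

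**Inputs assumed.** The rate of return of end-of-session forms and its dependence on the control-day score are not in the article. Return is set at 100/120 = 83%, with 70% as a variant. The acceptance rate above 80% in Section 3.1 concerns agreeing to take part, not returning the second form. The odds of non-return are multiplied by 1, 1.5, 2 or 3 per SD of control-day score; reversing the direction only reverses the sign of the bias.

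**Step 1: reproduce the plan's figures.** The SD of the difference is SD × √(2(1 − rho)), which equals SD at rho 0.5. The normal approximation is (1.960 + 1.645) × SD / √100:
- decision latitude: 3.605 × 0.644 = 2.32
- psychological demand: 3.605 × 0.407 = 1.47
- social support: 3.605 × 0.321 = 1.16

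The noncentral t version (99 degrees of freedom) gives 2.344, 1.482 and 1.169 against the stated 2.35, 1.48 and 1.17. The figures reproduce, which confirms the SD and correlation inputs.

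**Step 2: bias with no true change.** With equal means and SDs on both occasions, and return depending only on the control-day score X:

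expected change in complete pairs = (1 − rho) × (overall mean of X − mean of X among returners)

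At rho 0.5, half of the selection shift appears as change. For odds ×2 and 83% return, the simulated bias of 0.053 SD corresponds to a shift of 0.053 / 0.5 = 0.106 SD, and 0.0532 × 6.44 = 0.34 latitude points.

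**Step 3: simulation.** 120 enrolled, rho 0.5, no true change, 20,000 replicates per setting. The paired t-test is compared with a two-occasion normal likelihood that uses all control-day scores (equivalent to a mixed model with unstructured covariance). The Wilcoxon test was not simulated.

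| Return | Odds of non-return per SD | Bias (SD) | Bias (latitude points) | Paired t, type 1 error | All-data model, type 1 error |
|---|---|---|---|---|---|
| 83% | ×1 (no selection) | 0.00 | 0.00 | 5.0% | 5.0% |
| 83% | ×1.5 | 0.03 | 0.21 | 6.2% | 4.9% |
| 83% | ×2 | 0.05 | 0.34 | 8.4% | 4.9% |
| 83% | ×3 | 0.08 | 0.51 | 12.5% | 4.7% |
| 70% | ×1.5 | 0.06 | 0.38 | 8.5% | 5.1% |
| 70% | ×2 | 0.10 | 0.62 | 14.0% | 4.9% |
| 70% | ×3 | 0.13 | 0.87 | 23.6% | 4.9% |

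The bias of the all-data estimate is about 0 throughout. At 83% return, the paired-test bias is 0.21/2.35 = 9% to 0.51/2.35 = 22% of the stated detectable difference.

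**Step 4: sensitivity to the correlation (83% return, odds ×2).** Rho 0.3 gives 0.0756 × 6.44 = 0.49 points and 10.0% type 1 error. Rho 0.8 gives 0.0212 × 6.44 = 0.14 points and 6.3%.

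**The case against.** The strongest reply is that the remedy is already in the plan. The sentences after the test name random-effects models for the score and its evolution. A reader might infer that the whole analysis of the nightshift change rests on complete pairs. The article does not support that: it is true of the named test, not of the full set of analyses. What stands on the other side is that the models are introduced to complete the test and to look for explanatory factors. Nothing makes their occasion effect the reported result.

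A reader might also infer that the nightshift result will be biased. The article gives no return rate and no sign that return depends on the score. The envelope is mentioned in the first-phase paragraph, investigators assess the second-phase questionnaires, and Section 3.2.8 confirms posting of saliva only. Loss of end-of-session forms is plausible but not documented.

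The absence of a missing-data rule is no finding, since an article commonly leaves it to the full protocol or analysis plan. The point concerns only the stated choice of test.

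The correlation of 0.5 is a planning value. Section 1 describes the Karasek score as meant to capture a stable perception of work, which would favour a higher correlation and a smaller bias. Finally, the objective is secondary. These points all stand and limit the weight of the concern; none is a reason to prefer the paired test as the main analysis.

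**Conclusion.** The point holds as a cheap improvement to a stated method, not as a demonstrated error. The direction of the argument is algebra; its size depends on assumed return and selection. At 83% return and rho 0.5, odds of non-return changing 1.5- to 3-fold per SD give about 0.2 to 0.5 latitude points of false change and 6% to 13% type 1 error. A higher correlation shrinks this, lower return enlarges it, and no selection removes it. All these biases are well below the stated detectable difference of 2.35. The primary descriptive analysis is not affected, and the sample-size figures reproduce.

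The all-data model matches the paired test's error rate when there is no selection and keeps about 5% when return depends on the observed control-day score. It relies on data being missing at random. If return depends on the unobserved end-of-session state, such as exhaustion after the shift, it does not remove the bias.

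**What to change.** In Section 3.3, for this secondary objective:

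- Make the random-effects model the main test of the short-term change in each dimension, with occasion as fixed effect, participant as random effect, and every worker with a control-day score included whether or not the end-of-session form is available. Letting the residual variance differ between occasions matches the likelihood used in the calculation above.
- Keep the paired t-test or Wilcoxon test on complete pairs as a check.
- Report the number of returners and non-returners and their control-day scores, so that the size of any selection can be seen.
- State that the model assumes missing at random and does not cover return that depends on the unobserved end-of-session state.

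The cost is a few sentences of analysis wording. No new data, visits or change in sample size are needed.

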#### 3.2.8. Biological Samples

Several assays will be performed on the saliva sample. Biological analyses will be conducted by the Institute of Occupational Medicine of the Medical School of Clermont-Ferrand. We will measure salivary cortisol concentrations, DHEA-S, sIgA, and lysozymes. These parameters have been reported in the literature as correlated with the level of stress or workload. Only steroids (cortisol and DHEAS) with good stability will be measured in both samples. Peptides (sIgA and lysozyme) will be measured only during the dayshift (control). The samples made after the work session will be sent by post, which does not guarantee sIgA and lysozyme preservation.

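### The plan wants changes in questionnaires related to changes in biomarkers, but names no within-worker analysis for this, and a single-slope random-effects model would blend between-worker and within-worker associations

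*Protocol article*

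**What the plan says.** Protocol article, section 2.2 (Study Settings), gives the purpose of the two-phase design: "This will permit the evaluation of the relationships between modifications in questionnaire answers and biological responses". The contrast it sets up is the control day against the close of a shift that covers the night. This is a question about change within the same worker.

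Section 3.3 (Data Analysis) offers these tools:

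- For two variables together: "A correlation matrix analysis on quantitative variables (i.e., Karasek questionnaire and other psychological questionnaires) will be conducted using Pearson or Spearman correlation coefficients", with a principal component analysis.
- For the change in each Karasek dimension: it "will be tested with a paired two-sample Student’s test, or nonparametric Wilcoxon test if necessary".
- For explanatory factors: "Linear regression models and random-effects models will complete these analyses". With covariates, these models are meant "to seek possible explanatory factors of the Karasek score (a dayshift (control) versus the end of 24 h or shift) and its evolution".
- The same plan is extended to continuous parameters collected on both occasions, with the biological samples as the example.

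Section 3.2.8 (Biological Samples) limits what can be compared over time: "Only steroids (cortisol and DHEAS) with good stability will be measured in both samples". Salivary IgA and lysozyme are assayed on the control day only. The end of section 1 (Background) adds a broader aim, to explore associations of the Karasek score with stress biomarkers, without confining it to change.

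**The concern.** The paired tests describe the mean change of one variable at a time, so they cannot show whether two variables change together. Of the named tools, the regression and random-effects models are those directed at explaining the Karasek score and its evolution.

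A covariate measured on both occasions varies in two ways: between workers, in their usual level, and within a worker, from the control day to the end of the session. A random-effects model with one slope for it assumes that both kinds of variation have the same relation to the outcome. If they do not, the slope is a weighted average of the two.

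Workers with lastingly high strain and lastingly high cortisol could then produce a significant coefficient although nothing moves together across the nightshift. Read against the section 2.2 aim, that coefficient would look like a stress response to the shift. The reverse can also happen: a real within-worker response can be diluted by a between-worker association of the opposite sign.

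**Working it through.** **Inputs from section 3.1.** n = 100; two-sided 5%; power 95%; correlation 0.5 between the paired Karasek scores; pilot SDs 6.44, 4.07 and 3.21.

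**The plan's own figures.** SD of the difference = SD × √(2(1 − 0.5)) = SD. The normal formula (1.960 + 1.645) × SD/√100 gives 2.322, 1.467 and 1.157. The noncentral t with 99 df gives 2.344, 1.482 and 1.169, against the stated 2.35, 1.48 and 1.17. The figures reproduce. They concern mean changes in Karasek scores and say nothing about relating one change to another.

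**Assumptions added here.** Both variables have variance 1 and a repeat (intraclass) correlation of 0.5. Section 3.1 gives that value for Karasek scores only; for steroids it is assumed. The correlation ρ between workers' stable levels is not in the documents, so a range is shown. The true within-worker slope is zero.

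**Weight on the between-worker slope, two occasions.**

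- GLS factor: 0.5/(0.5 + 2 × 0.5) = 1/3.
- Covariate variation per worker: between 2 × (0.5 + 0.5/2) = 1.5; within 0.5.
- Weight: (1/3 × 1.5)/(0.5 + 1/3 × 1.5) = 0.5.

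Half of the coefficient is therefore between-worker. The slope relating worker means is 0.5ρ/0.75 = 0.667ρ, so the blended slope is about 0.5 × 0.667ρ = ρ/3.

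**Approximate test.** SE of the blended slope = 1/√(100 × (0.5/0.5 + 1.5/1.5)) = 1/√200 = 0.071. At ρ = 0.3, z = 0.100/0.071 = 1.41, and the chance of significance is about Φ(1.41 − 1.96) = 0.29.

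**Simulation.** 2,000 data sets per row, with a phase effect, a random-intercept model with one slope, and change-on-change regression:

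| Assumed ρ | ρ/3 | Mean simulated slope | Random-intercept, p < 0.05 | Change-on-change, p < 0.05 |
|---|---|---|---|---|
| 0 | 0 | −0.002 | 5.6% | 3.9% |
| 0.2 | 0.067 | 0.067 | 15% | 3.9% |
| 0.3 | 0.100 | 0.102 | 31% | 3.9% |
| 0.4 | 0.133 | 0.138 | 52% | 3.9% |
| 0.5 | 0.167 | 0.177 | 72% | 3.9% |
| 0.6 | 0.200 | 0.218 | 87% | 3.9% |

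The last column is constant because every row uses the same random draws, so it is one estimate of a nominal 5% rate. A plain correlation of control-day values is significant in 15%, 30%, 52%, 71% and 87% for ρ = 0.2 to 0.6. In this setting the blended slope is thus significant about as often as a correlation that contains no change at all.

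With a repeat correlation of 0.7, the random-intercept rates for ρ = 0.2 to 0.6 are 22%, 45%, 71%, 89% and 98%.

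**Masking, as an illustration only.** With a within-worker correlation of 0.3 and ρ = −0.4, power is about 20% for the blended slope and about 86% for change-on-change. The second figure follows from Fisher's transformation: atanh(0.3) × √97 = 3.05, and Φ(3.05 − 1.96) = 0.86. Nothing in the documents indicates opposite signs.

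**The case against.** The strongest reply is that section 3.3 does not exclude the right analysis. Its models target the Karasek score and also its evolution, so change is a declared target. Regressing the Karasek change on the steroid change would fit that sentence, and so would a random-effects model with worker-mean centring. This is a journal article, and how a time-varying covariate is coded is commonly left to a fuller document. The aim is secondary, and the primary analysis is mainly descriptive.

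Much of this stands. A reader might infer three stronger faults, and the text supports none of them:

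- *That the plan analyses levels.* No sentence says so, and the evolution of the score is named. The text leaves the choice open.
- *That the correlation matrix is the biomarker analysis.* It is described for the Karasek and other psychological questionnaires. The later extension to continuous parameters could be read as bringing biomarkers in, but that is not the only reading.
- *That the two occasions are stacked as independent rows.* This is planned nowhere; paired tests, the Stuart-Maxwell test and random effects are all named.

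A non-zero blended slope is also not wrong in itself. The broader association aim in section 1 can properly be served by a between-worker estimate. The simulated rates are false positives only if the coefficient is read as a within-worker response. Section 1 itself cites a study of neonatal professionals in which cortisol and stress questionnaires were not correlated, so the true between-worker correlation may be small.

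What the reply does not remove is that naming evolution as a target does not settle how a steroid enters the model. Evolution is usually modelled as a phase effect or a phase-by-covariate interaction, and a steroid entered as a raw covariate still carries one blended slope.

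**Conclusion.** The point holds as a gap between a stated aim and the methods named for it, with an inexpensive improvement available. Section 2.2 asks about changes that go together; section 3.3 names no analysis that isolates this; and the covariate-adjusted random-effects model that it does name would, with one slope per session-varying covariate, blend two associations.

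For ρ of 0.2 to 0.5 and a repeat correlation of 0.5, such a slope is significant in about 15% to 72% of studies with no within-worker link, against 4% to 5% for change-on-change. At ρ = 0 there is essentially no inflation. The size depends on assumed values of ρ and on carrying the 0.5 over from Karasek scores to steroids. The mechanism does not depend on them.

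Among the biomarkers, the change question can be answered only for cortisol and DHEA-S. Salivary IgA and lysozyme can support between-worker associations only. The primary analysis is not touched.

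**What to change.** In section 3.3, add for every covariate measured on both occasions (cortisol, DHEA-S, food intake):

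1. Enter the participant's mean and the deviation from that mean as two separate terms, together with a phase term. Alternatively, regress the Karasek change on the steroid change from control day to end of session.
2. Use only the deviation (or change) term to answer the section 2.2 question.
3. Report the mean term as a between-worker association, which serves the general association aim in section 1.
4. State that salivary IgA and lysozyme, measured on the control day only, are analysed for between-worker association only.

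The cost is one extra model term per covariate and a few lines of text, with no new data. The within-worker estimate may be less precise. Under the assumptions used here its standard error is 1/√(100 × 0.5/0.5) = 0.100 against 0.071 for the blended slope, about 1.4 times as large.

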#### 3.2.6. Occupational Characteristics

These include seniority (within the hospital, within the Emergency Department, and as an emergency occupation), current position (physician, internship or externship student, nurses, caregivers, cleaners, secretary, hospital porter, other), and type of contract (permanent or temporary). For physicians, these characteristics also include the type of emergency diploma or initial specialty and more details on contracts (professors, senior lecturer, hospital practitioner, assistant).

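### Seniority, a duration, is classed as categorical for chi-squared or Fisher testing, and no stated analysis uses it as a continuous variable; the usual power loss is moderate

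*Protocol article*

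**What the plan says.** Section 3.3 of the protocol article pairs seniority with gender: "The comparisons involving categorical parameters (gender, seniority) will be made with the Chi-squared test" or Fisher's exact test. Section 3.2.6 describes what is collected: "These include seniority (within the hospital, within the Emergency Department, and as an emergency occupation". It gives no unit and does not say whether the answer is a number of years or a band.

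The same analysis section treats the Karasek scores differently. For scores it says "The comparisons for quantitative parameters (e.g., biological data, questionnaires’ scores) will be based on" Student's t-test or the Mann–Whitney test. It adds that "Linear regression models and random-effects models will complete these analyses", and that these models, with covariates, serve "to seek possible explanatory factors of the Karasek score" and its change. Each Karasek dimension is also to be described "as quantitative and categorical variable". Section 3.1 names the cut-offs: "If we consider the different dimensions score as categorical (<> 71 <> 20 and <> 24".

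**The concern.** Length of service is measured on a time scale. Grouping it treats people inside a band as identical and makes the result depend on where the bands are cut. Section 3.3 makes this a stated rule, so it is more than a detail left open for an analysis plan.

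None of the analyses in section 3.3 clearly undoes the rule:

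- The correlation matrix is described as covering the Karasek and other psychological questionnaires, which leaves seniority out.
- The t-test and Mann–Whitney test compare two groups, so with these tests a categorical seniority becomes a two-way split.
- The regression models could take seniority in years, but the only statement about its form calls it categorical.

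What is at stake is power in the secondary search for factors that explain how emergency staff perceive their work. Seniority is one of the two examples the section gives of a characteristic to be compared.

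**Working it through.** **The plan's own figures.** The article gives no power for seniority. The nearest figures in section 3.1 are reproduced first.

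- Paired minimum differences. Inputs: n = 100, two-sided 5%, power 95%, correlation 0.5, SDs 6.44, 4.07 and 3.21. The SD of a difference is SD × √(2 × (1 − 0.5)) = SD. The normal approximation (1.960 + 1.645) × SD / √100 gives 2.32, 1.47 and 1.16. The noncentral t gives 2.34, 1.48 and 1.17. The article states 2.35, 1.48 and 1.17, so these are reproduced.
- Five predictors with power above 80%. The noncentral F with 5 and 94 degrees of freedom gives power 0.78, 0.81 and 0.84 at f² = 0.13, 0.14 and 0.15. The claim is attainable, but the article states no effect size.

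**Power for seniority against a Karasek score.** Inputs from the article: n = 100, two-sided 5%, and 6% of pilot decision latitude scores above 71 (94% of demand scores were above 20). Assumptions: seniority and score are bivariate normal, with true correlation r = 0.2, 0.3 or 0.4. Each score is r × seniority + √(1 − r²) × noise. There were 4,000 replicates per r, so the Monte Carlo standard error is at most √(0.25 / 4,000) = 0.008.

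| Seniority | Karasek dimension | Test | r = 0.2 | r = 0.3 | r = 0.4 |
|---|---|---|---|---|---|
| Continuous | Continuous | Correlation or slope | 0.52 | 0.87 | 0.99 |
| Four ordered bands | Continuous | Linear trend | 0.45 | 0.81 | 0.97 |
| Median split | Continuous | t-test | 0.35 | 0.68 | 0.90 |
| Four bands | Continuous | Analysis of variance | 0.31 | 0.65 | 0.91 |
| Median split | Median split | Chi-squared | 0.30 | 0.56 | 0.80 |
| Four bands | Median split | Chi-squared | 0.22 | 0.46 | 0.74 |
| Median split | Cut at 6%/94% | Chi-squared | 0.11 | 0.20 | 0.33 |
| Median split | Cut at 6%/94% | Fisher | 0.04 | 0.08 | 0.16 |

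**Check by formula.** Power is approximately Φ(atanh(ρ) × √97 − 1.96).

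- Both continuous, ρ = r = 0.3: 0.3095 × 9.849 − 1.96 = 1.088, so power is 0.86 (simulated 0.87).
- Median split of seniority, ρ = r × √(2/π) = 0.3 × 0.798 = 0.239: 0.2441 × 9.849 − 1.96 = 0.444, so power is 0.67 (simulated 0.68).

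The factor 2/π = 0.64 is the share of information that a median split keeps.

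**Check with no association (r = 0).** Rejection rates were 0.052 for the correlation, 0.050 for the median-split t-test, 0.072 for the chi-squared test with both variables split at the median, and 0.011 for Fisher at the 6%/94% cut. So the median-by-median chi-squared powers are slightly flattering, and Fisher is very conservative in so unbalanced a table.

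**Why the last two rows are extreme.** At 6% prevalence, 100 people give about 6 on the rare side. For social support, where the pilot had 100% above 24, the same pattern would leave one column empty and nothing to test.

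**The case against.** A reader might infer that chi-squared or Fisher is the planned test of seniority against the Karasek scores, that the scores are therefore forced into categories, and that a real association would usually be missed. The article does not support this. The same section sends questionnaire scores to the t-test or Mann–Whitney test and plans linear and random-effects models for explanatory factors of the Karasek score. Section 3.1 supports that objective with its five-predictor statement. A contingency-table test reaches Karasek only in the additional categorical presentation of each dimension.

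The lowest powers also stack several conditions. They need a median split of seniority, which the article does not specify, and Karasek tested as a dichotomy. They also need a prevalence taken from 19 physicians at one hospital, although the cohort is multicentre and includes nurses, caregivers, secretaries, porters and others. Section 3.2.1 moreover mentions analysis based on the median of each factor, which would give more balanced groups. Finally, an article may leave the coding of covariates to a fuller document.

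All of this stands as a limit on the size of the problem. It does not remove it. The article says how seniority is to be classed and says categorical; nothing in section 3.3 says that seniority enters any analysis as a duration.

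**Conclusion.** The point holds as a minor one. Section 3.3 classes a duration as categorical, and no route it states uses seniority as a continuous variable. With the Karasek scores kept quantitative, the usual loss is moderate: at r = 0.3, from 0.87 to between 0.65 and 0.68 when seniority is banded, or to 0.81 if a trend over four ordered bands is tested. The loss becomes severe only where a Karasek dimension is also cut near the pilot's 6%/94% prevalence. It is nil if the regression takes seniority in years.

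These figures rest on an assumed correlation, bivariate normality and 100 analysed participants. Real seniority is likely to be skewed, so they show the order of the loss and are not predictions. The primary analysis is descriptive and is not affected.

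**What to change.** - Remove seniority from the categorical examples in section 3.3, and limit chi-squared and Fisher to truly categorical variables.
- State in section 3.2.6 that each of the three seniority measures is recorded in years.
- Analyse seniority as continuous against the continuous Karasek dimensions: Spearman correlation, and a linear or simple spline term in the regression models already planned.
- Keep seniority bands for descriptive tables.

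The cost is a wording change. If the form now collects seniority in bands, one item on it must change as well. No extra participants, visits or samples are needed.
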